**Figure 2 figure2:**
[figure not shown]
IePRO (immune-related adverse events monitoring through electronic patient-reported outcomes) Model of Care: (1) When prompted by the mobile app, patients reply to a Patient-Reported Outcomes version of the Common Terminology Criteria for Adverse Events symptom questionnaire via their own computer or mobile device. Data collected through the questionnaire are stored in a server controlled by the study sites. (2) Triage nurses are notified when patients have declared symptoms. (3) In the event of new or worsening symptoms, nurses initiate a telephone triage call with the patient. (4) Using the United Kingdom Oncology Nursing Society 24-hour triage tool, nurses determine the adequate course of action according to symptom severity and communicate the outcome of their assessments with the clinical team. The triage nurse's detailed assessment is recorded in a triage log stored in the electronic health record. EHR: electronic health record; ePRO: electronic patient-reported outcome; PRO-CTCAE: Patient-Reported Outcomes version of the Common Terminology Criteria for Adverse Events.

Triage nurses perform an assessment of the reported symptoms with the United Kingdom Oncology Nursing Society 24-hour triage tool [44], which are graded on a CTCAE-based scale [45]. If patients report symptoms not covered by the PRO-CTCAE questionnaire, they are also addressed during these calls. The combination of symptoms may result in different types of color-coded alerts that tie into different recommendations. Mild symptoms generally result in green alerts, where self-care and self-monitoring instructions are warranted. Moderate symptoms requiring remote follow-up within the next 24 hours correspond to an amber alert. The presence of 2 or more amber alerts or of severe symptoms results in a red alert, where urgent in-person assessment is recommended. Triage nurses communicate with physicians via email or telephone according to the type of alert. A triage log detailing the symptom assessment, recommendations to the clinical team, and the actions taken to manage patient care is added to the electronic health record (EHR).

Patients are informed that this model of care is complementary to the usual care model. They are instructed by the triage nurses and subinvestigators in the clinical team that in the event of a symptom that causes them any level of concern and would lead them to seek medical assistance, they must contact their reference clinician or the on-call oncologist as usual. It is also clarified that the likelihood of being called by the triage nurse should never delay them from seeking medical assistance. In this sense, patients are reminded of these procedures at every telephone interaction with the triage nurses.

### Electronic App (Medical Device)

This study is categorized as a clinical trial with medical device of risk category A1. It uses a web-based and mobile CE-marked app (Kaiku Health app) containing the PRO measures. The app is classed as a medical device that allows patients to submit their answers and access previous replies. Patients receive a summary of the reported symptoms detailing which of those improved, remained stable, or worsened. The app’s security features were assessed and validated by the participating hospitals’ information technology departments. Web-based and mobile versions of the app are identical in content and functionality. Patient data collected through the medical device are encrypted at rest and in transit and are subject to regular backups. Security updates are ensured by the app developer (Elekta AB). Two-factor authentication is activated for all patients.

### Study Objectives and Outcomes

#### Primary Objective and Primary Outcome

The primary objective of the IePRO RCT is to compare the effect of an ePRO-based model of care to the current standard model of care on the delay between symptomatic IrAE onset and its detection by health care providers in patients with cancer treated with ICIs. The ePRO-based model of care complements the standard model of care with remote symptom monitoring via ePROs and remote symptom management via telephone triage calls done by oncology nurses. The primary outcome is the time-to-detection of IrAEs, as evidenced by a statistically significantly lower length of time when compared to that in usual care. Time to detection is the difference expressed in days between the IrAE detection date by the clinical team and the associated symptom’s onset date according to the patient’s self-report.

#### Secondary Objectives and Secondary Outcomes

The secondary objectives of this trial include assessing the effect of the ePRO-based model of care on the following secondary outcomes: (1) the delay between symptom onset and deployment of pharmacological interventions to manage symptomatic IrAEs by a statistically significant shorter or longer average time delay, (2) the type and amount of pharmacological interventions to manage symptomatic IrAEs by a statistically significant lower average dose, (3) the average maximum symptomatic IrAE grade by a statistically lower or higher average score, (4) the HRQoL through a statistically significant higher or lower overall score of the Functional Assessment of Cancer Therapy-General (FACT-G) questionnaire [46], (5) the perceived self-efficacy to manage symptoms through a statistically significant higher or lower score of the PROMIS (PRO Measurement Information System) Self-Efficacy for Managing Chronic Conditions–Managing Symptoms (short form 8a) [47], (6) overall survival at 6 months plotted using Kaplan-Meier estimates, using routine data collected in the EHR, and (7) description of the symptomatic IrAEs experienced by patients by type and grade according to version 5.0 of the National Cancer Institute’s CTCAE [48]. Remote symptom management processes recorded by nurses will be described using (1) patient-reported symptoms triggering remote symptom management procedures using the composite grading algorithm for the PRO-CTCAE questionnaire [49] and (2) the type of issued triage alerts following triage procedures according to the United Kingdom Oncology Nursing Society 24-hour triage tool [44] and associated symptoms reported using the PRO-CTCAE questionnaire.

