## Introduction

Immune checkpoint inhibitors (ICIs) have increasingly become part of the standard treatment for multiple cancer types and stages, with the main benefits including superior overall survival rates [1-14]. Although ICIs are generally considered as well-tolerated, they may trigger immune-related adverse events (IrAEs), which can be severe and result in debilitating or fatal outcomes [15,16]. Treatment modality, cancer type, and patient characteristics appear to influence the likelihood of symptomatic IrAEs, which generally occur in 40%-80% of patients [10,15]. Combinations of ICI agents generally result in a higher incidence and severity of symptoms, with 55% of IrAEs being severe (grade 3 or higher) [15,17]. Even though the incidence of IrAEs appears to be positively correlated with superior objective response rates to ICIs, the occurrence of severe events may lower overall survival rates [2,18]. It is posited that solid tumors that exhibit high mutational burden elicit a stronger immune response, which may trigger more IrAEs [19,20]. Limited evidence suggests that skin, respiratory, renal, and hepatic IrAEs also appear to be correlated with melanoma, lung cancer, kidney cancer, and hepatocellular cancers, respectively, suggesting that different tumor types may increase the likelihood of specific IrAEs [21-23]. In addition, genetic risk factors such as allelic variations of *HLA-B* and mutations in the *TMEM162* gene are correlated with higher or lower likelihood of IrAEs [24]. Recent studies have highlighted that the potential chronicity of IrAEs could further burden patients and contribute to lower overall quality of life [16,25-27]. The timing of detection and intervention of IrAEs appears to play a key role in limiting their progression and outcome [10,15,28].

Although most IrAEs occur within the first 3-6 months of the start of treatment, some may develop after a year even when treatment has been discontinued [15,29,30]. In addition to the uncertainty of when they may manifest, IrAEs are heterogenous in their symptomatic presentation and are usually related to the affected tissue or organ [15]. Therefore, patients need to be ready to engage in self-care activities to self-monitor and self-manage symptoms they confront outside of the clinical environment during the multiple weeks between treatments [31].

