### Intervention

The intervention of this RCT consists of a complementary model of care that uses ePROs to facilitate remote symptom management [42]. This model is represented in Figure 2. Patients in the intervention arm have access to a weekly PRO-CTCAE questionnaire through an electronic mobile app. Patients receive an email invitation to access the app and an information sheet explaining its interface. Once patients access the app, they are required to complete a questionnaire of predefined symptoms. During the first 3 months of the intervention, active symptoms are reassessed daily. When replying to a questionnaire, patients can add any other item of the full PRO-CTCAE item library, which are automatically added to the following daily or weekly questionnaires as well (see Multimedia Appendix 2). The rapid and sudden onset of IrAE and ICI’s interference with pre-existing conditions and symptoms drove the decision to collect symptom data daily [10,28]. Due to the potential burden this sustained frequency could represent to patients, this was restricted to the first 3 months of the intervention. Patient replies are available in real time to the triage nurses. Two triage nurses at each site are notified via email when patients submit new replies or report severe symptoms, and they contact patients by telephone in the event of new or worsening symptoms. The nurses review patients’ answers every working day from 8 AM to noon. Outside of these hours, usual care procedures apply.

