Dropping tumor type and excluding ICI agents as stratification criteria constitute a major limitation of this study, as patient groups could present important differences that could influence the type, severity, and frequency of IrAEs. This consideration should guide future analysis of the data, and its impact will be addressed in future publications. More frequent measuring and the reactive nature of the intervention increase the risk of surveillance bias, as clinicians will be more aware of the challenges patients are experiencing. The intervention also does not allow blinding of patients who may alter their usual self-monitoring and self-care behaviors due to their awareness of the triage nurse’s monitoring [66]. As this study is being deployed in 2 sites, tracking hospitalization and emergency room admissions for patients in the control group was outside the resources available to the study team. As a consequence, they were not included as secondary end points for this study, limiting insight on its efficiency to improved care. Overall survival measures were capped at 6 months due to limited resources to pursue a longer target, which could hinder the visibility of long-term effects of the model of care. Lastly, excluding patients who self-declare unable to use the electronic app and the lack of alternative means to self-report symptoms limit the comparability of this sample to the general population [36,67]. Despite these limitations, the IePRO RCT takes a pragmatic approach to symptom monitoring with ePRO data by not insulating its model of care from the existing resources the sites use to assist patients. Importantly, the IePRO RCT may further highlight the challenges patients treated with ICIs face outside the clinical setting, particularly as more data revealing the true burden of treatment-associated toxicities continue to emerge.

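### Secondary outcome 3 compares mean maximum IrAE grade among patients with a detected IrAE, so extra mild detection in the intervention arm could lower it without any fall in severity

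*Protocol article*

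**What the plan says.** Under Secondary Objectives and Secondary Outcomes, item 3 is "the average maximum symptomatic IrAE grade by a statistically lower or higher average score". No value is given for a patient who has no IrAE. Under Primary Objective and Primary Outcome, "The primary outcome is the time-to-detection of IrAEs", and "Time to detection is the difference expressed in days between the IrAE detection date by the clinical team" and the patient-reported onset of the associated symptom. A patient without a detected IrAE has no such difference. The Introduction says of symptomatic IrAEs "which generally occur in 40%-80% of patients".

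The Intervention section describes contact that only one arm receives. Its patients complete weekly symptom questionnaires, with daily reassessment of active symptoms for 3 months. Triage nurses review the answers, and "they contact patients by telephone in the event of new or worsening symptoms". Low-grade complaints are part of this pathway: "Mild symptoms generally result in green alerts, where self-care and self-monitoring instructions are warranted". The result reaches the health record: "A triage log detailing the symptom assessment, recommendations to the clinical team, and the actions taken to manage patient care is added". Data Collection Methods takes IrAE data in both arms from review of that record, specifically the oncologist's notes at scheduled appointments.

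The Discussion says that more frequent measuring and "the reactive nature of the intervention increase the risk of surveillance bias, as clinicians will be more aware" of what patients are experiencing. Statistical Methods adjusts the regressions for cancer type, age and treatment regimen.

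**The concern.** A mean maximum grade needs a grade. If it is averaged over patients with a detected IrAE, the two groups compared are no longer the randomised groups but those in whom an IrAE was found, and the finding is done differently in the two arms. A patient whose mild IrAE would pass unrecorded in usual care enters the average in the intervention arm at grade 1 and pulls it down. The planned covariates do not describe who becomes a detected case, so adjustment does not repair this. The trial could then report lower severity when it had only detected more mild events.

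The primary outcome is conditioned in the same way, but the consequence is less certain. Extra cases shorten the mean delay only if they are found faster than the average case.

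**Working it through.** **The plan's own figure.** Two-sided 5%, 90% power, SD 3.65, difference 2 days: n per arm = 2 × (1.960 + 1.282)² × 3.65² / 2² ≈ 70, so 140 in total (142 by the exact t test). The stated 138 is within 3% of both, and 138 / 0.7 gives 198. The SD comes from 29 records of patients who all had an IrAE, which supports reading the delay as conditional on having one. I use 138 analysed patients, 69 per arm, below.

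**Inputs.**
- From the article: mean delay 4.43 days, SD 3.65, target difference 2 days, IrAE incidence 40% to 80%.
- Assumed: usual care detects an IrAE in a share p = 0.50; mean maximum grade G = 2.0 among them; the intervention adds a share q = 0.10 to 0.15 of grade 1 cases found after d days; every IrAE that usual care would also find has the same grade and delay in both arms. There is thus no true effect.

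**Mean grade among detected cases.** Intervention mean = (p × G + q × 1) / (p + q).
- q = 0.10: (0.50 × 2.0 + 0.10) / 0.60 = 1.83, a fall of 0.17.
- q = 0.15: (0.50 × 2.0 + 0.15) / 0.65 = 1.77, a fall of 0.23.

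The fall equals q(G − 1) / (p + q). At p = 0.40 it is 0.20 to 0.27. At p = 0.80 it is 0.11 to 0.16. At p = 0.50 with G = 1.5 it is 0.08 to 0.12.

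**Effect on the test.** In a simulation of this null case (69 per arm, t test, two-sided 5%), a false finding of lower grade occurred in 14% of trials at q = 0.10 and 24% at q = 0.15, against 2.5% with no extra cases. A grade mix of 30/40/30% for grades 1/2/3 (mean 2.0) gives figures of this size. The proportion with grade 3 or higher among all randomised patients kept a two-sided error rate of about 5% throughout.

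**Scoring no IrAE as 0.** The mean over all patients is then p × G in the control arm and p × G + q × 1 in the intervention arm. Extra mild detection raises the intervention mean by 0.10 to 0.15. The bias reverses and does not disappear.

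**Delay.** Intervention mean = (p × 4.43 + q × d) / (p + q), so the shift is −q(4.43 − d) / (p + q).

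| d (days) | q = 0.10 | q = 0.15 |
|---|---|---|
| 1.5 | −0.49 | −0.68 |
| 3.5 | −0.16 | −0.21 |
| 4.43 | 0 | 0 |

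At d = 1.5 the shift is a quarter to a third of the 2-day target (0.49 / 2 = 0.24; 0.68 / 2 = 0.34). The simulated one-sided false-positive rate was then 15.3% and 20.4%. With d = 4.43 it stayed at 5% to 6%. For p from 0.40 to 0.60, q from 0.05 to 0.30 and d from 0.5 to 2 days, the shift runs from −0.19 to −1.68 days.

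**The case against.** **The mechanism is inferred.** Nowhere does the article say that the intervention will add mild, early cases. Both arms have the same number of scheduled appointments, and IrAE data come from the oncologist's notes in both. The triage log is not named as a source of IrAE data, and mild complaints usually lead to self-care advice. A reported symptom is not yet a recorded IrAE. This stands: the direction is plausible, given the one-sided screening and the conceded surveillance bias, but the number and mildness of extra cases are undocumented.

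**Item 7 already describes IrAEs by type and grade.** An excess of grade 1 events might show there. But the item does not say by arm, and a description does not correct the test in item 3.

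**The analysis set belongs in the analysis plan.** In part this is so, and the article does not say that patients without an IrAE are left out of the mean. But the article itself fixes the outcome as a compared average grade. Left out or scored 0, patients without an IrAE make that average depend on how hard each arm is searched. Only the direction changes.

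**A stronger reading is tempting:** that delay and grade are equally compromised, and that both will improve with no real benefit. The documents do not support it. The delay bias vanishes if extra cases take as long to find as the others. Earlier detection is also the stated objective: finding an IrAE that usual care would never detect is the intended effect, and leaving such a case out of the control arm flatters that arm.

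**Conclusion.** The point holds for secondary outcome 3. Read naturally, it compares groups formed after randomisation by a detection process that differs between arms, and neither the covariates nor the acknowledged limitation corrects this. The size, a fall of 0.17 to 0.23 grade under no effect, rests on the assumed 50% incidence, mean grade 2.0 and 10 to 15 points of extra grade 1 cases. It illustrates what could happen and does not forecast it.

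For the primary outcome the point is weaker: the conditioning is the same, but the bias lies anywhere from nil to about 0.7 day in the central illustration, depending on an unknown detection speed. That calls for fuller reporting and cautious interpretation, not a new primary outcome. This is an inexpensive improvement that should be made.

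**What to change.** **Secondary outcome 3.** Make the between-arm test the proportion of all randomised patients with a grade 3 or higher symptomatic IrAE by 6 months, counting a patient with no IrAE as not having the event. Keep mean maximum grade among detected cases as descriptive only. Do not use a mean or ordinal score with no IrAE set to 0 as confirmation, because extra mild detection biases it the other way.

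**Primary outcome.** Report the number and proportion of patients with a detected IrAE by arm and grade beside the delay result. Show delay in grade 2 or higher IrAEs as a sensitivity analysis with its estimate and confidence interval, and note that this subset is also formed after randomisation. Interpret a shorter delay with caution if the excess in the intervention arm is mainly grade 1. A rule that the sensitivity analysis need only agree in direction should not be used: in the simulated null case it cut false positives only from 15.3% to 14.9% and from 20.4% to 19.3%.

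**Cost.** Grades are already collected, so this is a change of wording. The price is precision. If 50% have an IrAE and 30% of those reach grade 3 (assumed), the event rate is 0.50 × 0.30 = 15%, about 10 patients in an arm of 69. The 95% interval for the difference is then roughly ±1.96 × √(2 × 0.15 × 0.85 / 69) = ±12 percentage points. Data collection stops at withdrawal, so a rule is also needed for patients who leave before 6 months.

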#### Exploratory Objectives

As exploratory objectives, the RCT will also describe the following in the intervention group: (1) symptoms reported via the PRO-CTCAE questionnaire that suggested the need for in-person intervention and patients received the intervention (true positives), (2) symptoms reported via the PRO-CTCAE questionnaire that suggested the need for in-person intervention but patients did not receive the intervention (false positives), (3) type of interventions required and provided for symptoms as reported in the triage log and the EHR, (4) symptoms reported via the PRO-CTCAE questionnaire that require an intervention beyond remote symptom management, (5) usability of the electronic app used to collect PRO symptom data and acceptability of the ePRO-based model of care, assessed through semistructured patient interviews, and (6) acceptability of the ePRO-based model of care assessed via semistructured individual interviews and focus groups with clinical nurse specialists, nurses, and physicians.

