Other limitations of this study are that the broad triggers for a telephone triage call (new or worsening symptom) may lead to a significant number of calls that may not always result in meaningful changes to how care is provided. A recent publication by Msaouel et al [64] has described adaptive and more granular alert thresholds that could prevent and alleviate clinician burden. Clinicians in similar studies have noted the time-consuming nature of ePRO data review, and these broad triggers may compound that burden further and limit clinician compliance to study procedures [65]. Tolstrup et al [66] attempted to empower patients with the decision to contact the hospital, though this may have discouraged computer-naïve patients from doing so even when symptoms were concerning, leading the authors to consider a proactive approach for future iterations of remote PRO monitoring. Integration with the EHR was complicated by the differences in EHR platforms across study sites and the short time interval between the finalized code for the mobile app and the start of the study. EHR integration is a major factor for ensuring successful implementation of ePRO monitoring [63], and it remains unclear if the measures implemented to mitigate the lack thereof will be successful.

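### The exploratory true- and false-positive labels are defined by whether in-person care was received, so they record whether symptom reports were acted on, not whether they were accurate

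*Protocol article*

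**What the plan says.** The protocol article, under Exploratory Objectives, states that "the RCT will also describe the following in the intervention group". Item 1 covers symptoms reported through the PRO-CTCAE questionnaire that "suggested the need for in-person intervention and patients received the intervention (true positives". Item 2 covers those that "suggested the need for in-person intervention but patients did not receive the intervention (false positives". Both definitions start from the same kind of report and differ only in whether care was received.

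Item 3 of the same list is the "type of interventions required and provided for symptoms as reported in the triage log and the EHR". It names need and receipt separately but is not linked to the labels in items 1 and 2.

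The Intervention section describes how a report can lead to care. A nurse telephones the patient and assesses the symptoms with a triage tool on a CTCAE-based scale. The outcome may be a coloured alert: "The presence of 2 or more amber alerts or of severe symptoms results in a red alert, where urgent in-person assessment is recommended". Then "Triage nurses communicate with physicians via email or telephone according to the type of alert".

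Statistical Methods assigns descriptive statistics to exploratory outcomes.

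**The concern.** True positive and false positive are accuracy terms. They presuppose a reference for the condition of interest, which here is a real need for in-person care, established separately from the result being judged. The stated definitions use receipt of care instead, and this fails in two ways.

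- **Receipt depends partly on the report.** The report prompts the nurse call, and the triage result, with its recommendation, goes to the physicians. Care given because the report was made then counts as confirmation of the report.
- **Non-receipt does not show absence of need.** The patient may decline or not attend, or a clinician may not respond. A justified report that is not acted on is labelled false.

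A reader of the results would take the two counts as evidence on how often the questionnaire raises false alarms. The counts cannot support that reading.

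**Working it through.** The plan states no figure to reproduce. The check is of the definition itself, followed by an illustration with assumed rates.

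**1. What the labels depend on.** Among reports that suggested in-person need there are four combinations:

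| | Care received | Care not received |
|---|---|---|
| Need real | labelled true positive | labelled false positive (wrong) |
| Need not real | labelled true positive (wrong) | labelled false positive |

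The definitions use only the column. No confirmed IrAE, CTCAE grade or judgement of need enters, and no other section supplies one for these labels.

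**2. General form.** Let π be the share of such reports with genuine need, a the probability that care is received given need, and b the probability that it is received given no need.

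- Labelled true-positive share = πa + (1 − π)b. The share with real need is π.
- Share of labelled false positives with genuine need = π(1 − a) / [π(1 − a) + (1 − π)(1 − b)].
- Share of labelled true positives without need = (1 − π)b / [πa + (1 − π)b].

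When reports with and without need both occur, every label is right only if a = 1 and b = 0.

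**3. Illustration.** All values of π, a and b are assumptions; the documents give none.

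- π = 0.60, a = 0.70, b = 0.20. Labelled share = 0.42 + 0.08 = 0.50, against 0.60. Labelled false positives with need: 0.18 / (0.18 + 0.32) = 36%. Labelled true positives without need: 0.08 / 0.50 = 16%.
- π = 0.90, a = 0.50, b = 0. Labelled share = 0.45, against 0.90. Labelled false positives with need: 0.45 / (0.45 + 0.10) = 82%.
- π = 0.30, a = 1.0, b = 0.50. Labelled share = 0.30 + 0.35 = 0.65, against 0.30. Labelled true positives without need: 0.35 / 0.65 = 54%.
- π = 0.30, a = 0.50, b = 0.20. Labelled share = 0.15 + 0.14 = 0.29, close to 0.30, yet 0.14 / 0.29 = 48% of the labelled true positives had no need.

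The error can run in either direction. The last case shows that an overall share can look right through cancellation while the individual labels are wrong. The counts of received and not received alone cannot tell a reader which case applies.

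**The case against.** The strongest reply is that the plan only describes these reports. It announces no predictive value, test or threshold decision, so there is no accuracy statistic to be biased. That is correct and limits the point to the labels and how they will be read.

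The second reply is that a professional assessment lies between report and care. A report that looks severe on the questionnaire, is downgraded on the telephone and leads to no visit may well be a real false positive of the questionnaire. This also stands. The circularity is partial, and some non-receipt will reflect true absence of need. A reader might infer that a red alert simply confirms itself, but the classified unit is the symptom report, not the alert, and the triage call adds information.

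Third, need is partly visible elsewhere. Item 3 covers interventions required as well as provided, and item 4 covers symptoms that call for more than remote management. It would therefore be too strong to say that unmet need disappears from the results.

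Two other strong readings also fail:

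- The Discussion says that "these broad triggers may compound that burden further and limit clinician compliance to study procedures". This is a possibility, raised about triggers for the telephone call. It is not a forecast that recommendations for in-person care will be ignored, and it does not establish that these labels would lead to higher thresholds and missed IrAEs.
- Reports made outside the nurses' review hours do not automatically become false positives. Usual care applies then, and patients are told to contact their clinician or the on-call oncologist, so in-person care may still follow.

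None of these replies supplies a reference for need in items 1 and 2.

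**Conclusion.** The concern holds as a fault in a stated definition. It is not a detail left to an analysis plan, because the article gives both definitions in full and neither refers to need. The labels measure whether a report was followed by in-person care, and accuracy cannot be read from them.

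The impact is minor. The outcomes are exploratory, descriptive and limited to the intervention group, and nothing in the primary or secondary analyses or the sample size depends on them. The numerical examples rest entirely on assumed rates and show only that the distortion could be large in either direction; they do not predict what the trial will find.

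**What to change.** Rename the two categories as in-person intervention received and in-person intervention not received, and state that no conclusion on accuracy or over-alerting will be drawn from them. This is a wording change and needs no new data.

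If true- and false-positive labels are kept:

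- base them on need as documented in the triage log and EHR, which is the required part of item 3;
- cross-tabulate required against provided, so that needed but not given and given but not needed are both shown;
- classify reports with no documented assessment as unverified, not as false.

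This takes some analysis work on sources the trial already plans to use. The accuracy description becomes less complete, because of the unverified group, and the reference is still unblinded, because those who document need know of the report.

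A clinician grade recorded by the next scheduled appointment would not be a clean substitute. It is also made with knowledge of the report, effective early care could lower it, and the article states CTCAE version 5.0 grading only for symptomatic IrAEs, so a grade is not assured for every reported symptom.
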